## Abstract

Sierra Leone faces persistently high neonatal and maternal mortality rates, driven largely by delayed recognition and treatment of newborn respiratory distress and postpartum hemorrhage. In this protocol, we describe the planned implementation of a bundle of maternal and newborn clinical practices over a 36-month period across nine public health facilities in the Greater Freetown area and Bo District to address these critical gaps. The service delivery improvements include the World Health Organization (WHO) Essential Newborn Care Course (ENCC) Parts 1 and 2; Vayu bubble continuous positive airway pressure (bCPAP) and oxygen blenders for respiratory support; the WHO Postpartum Hemorrhage package; and obstetric risk stratification using point-of-care ultrasound (POCUS) and complementary diagnostics for maternal care improvement. We anticipate that this bundle of evidence-based clinical tools and training, reinforced by mentorship, structured checklists, and low-dose high-frequency (LDHF) practice, will significantly reduce perinatal and maternal mortality and morbidity. The bundle will be evaluated using a Hybrid Type 1 effectiveness-implementation design, utilizing routine health information system data, supplemented by project registers, skills assessments, and observations. By aligning with the Ministry of Health’s Child Survival Action Plan, the aim of this project protocol is to provide a sustainable and scalable model for reducing preventable maternal and newborn deaths in resource-constrained settings.

## 1. Introduction

### 1.1. Background

Neonatal mortality (infant death within 28 days of birth) remains a significant health concern worldwide, accounting for nearly half of all deaths in children under five years of age, with the majority occurring in low-to-middle-income countries (LMICs) [1,2]. In Sierra Leone, the neonatal mortality rate (NMR) remains high at 31 per 1000 live births, far exceeding the Sustainable Development Goal 3.2 (SDG) target of 12 per 1000 [3,4]. Reducing neonatal mortality and morbidity is thus a high priority.

Neonatal respiratory distress is the leading cause of neonatal morbidity and mortality in the first week of life. Immediate recognition of respiratory distress, followed by prompt resuscitation and follow-on care, is critical for survival [5,6,7,8,9]. The results of previous studies have demonstrated that implementation of bundled newborn care interventions, including resuscitation training and respiratory support, can significantly reduce neonatal mortality. For example, the “Safer Births Bundle of Care” program in Tanzania, which implemented low-dose, high-frequency resuscitation training and skills mentoring for midwives, recently demonstrated a 40% reduction in neonatal deaths in the first week of life [10].

Continuous positive airway pressure (CPAP), delivered as either mechanical or bubble CPAP, plus oxygen blenders improve neonatal respiratory distress outcomes by preventing hyperoxic lung injury and retinopathy of prematurity. In a separate study from Tanzania, Vayu brand bubble CPAP (bCPAP) implementation was associated with immediate improvement in respiratory function [11]. While these and similar findings validate the hypothesis that bundling evidence-based clinical tools with skills mentoring and practice can drive rapid improvements in survival in high-burden settings, the implementation of advanced newborn care in Sierra Leone remains limited due to equipment shortages and gaps in provider training [12,13,14,15,16]. In light of the country’s position among the 15 countries with the highest NMRs worldwide, overcoming these barriers is an urgent priority.

Meanwhile, the maternal mortality rate (MMR) in Sierra Leone remains unacceptably high at 443 per 100,000 live births, placing it among the worst 15 countries worldwide [2,3,17]. Postpartum hemorrhage (PPH) is the leading global cause of maternal mortality and is particularly deadly in resource-constrained settings, where detection and treatment can be delayed [3].

Intrapartum complications, such as hemorrhage, labor dystocia, fever, abnormal lie, and fetal distress, may lead to perinatal asphyxia, worsening outcomes for both the mother and baby [18,19,20,21,22]. To mitigate these risks, the integration of obstetric ultrasound in LMIC maternity units has proven highly valuable [23]. Evidence indicates that routine ultrasound use significantly improves diagnostic accuracy and risk stratification for high-risk conditions, such as placenta previa, malpresentation, and multiple gestations, enabling timely referrals and appropriate clinical management before emergencies arise [23]. Thus, more effective recognition and treatment of hemorrhage, combined with enhanced maternal risk assessment and case management, can improve maternal outcomes.

The aim of this protocol is to describe a targeted newborn and maternal bundle that will be implemented in Sierra Leone, as shown in Figure 1. The newborn bundle combines improving and sustaining high-quality neonatal resuscitation with utilization of bCPAP for respiratory distress treatment. The maternal bundle combines improved intrapartum risk assessment with high-quality prevention and treatment of maternal hemorrhage.

### 1.2. Strategic Alignment and Policy Context

The bundle operationalizes two national frameworks, including the Sierra Leone National Health Sector Strategic Plan 2021–2025 and the Ministry of Health and Sanitation (MoHS) Child Survival Action Plan 2023–2025, both of which prioritize reductions in under-five and maternal mortality through strengthened newborn services [24,25]. The MoHS has established special care baby units in 16 districts and scaled up Helping Babies Breathe nationally [26]. Two implementation gaps remain. First, the more comprehensive WHO Essential Newborn Care Course (ENCC), particularly Part 2, covering the first 24 h of life has not been introduced [27]. Second, the WHO Postpartum Hemorrhage Package has not been operationalized as an integrated bundle linking blood-loss quantification, intrauterine balloon tamponade, and active management of the third stage of labor. This protocol addresses both gaps; Figure 1 maps each bundle component to its corresponding national policy objective.

The maternal component aligns with both the national plan and global best practices by implementing the WHO Postpartum Hemorrhage Package and transitioning care from simple management to a comprehensive PPH “bundle” approach. Innovative maternal triage and risk assessment strategies address potential upstream sources of intrapartum complications. Aligned with these national priorities, the primary objective of implementing this targeted bundle is to improve maternal and newborn outcomes. Figure 1 shows the alignment of the maternal and newborn bundle with national goals.

### 1.3. Implementation Logic Model

The implementation logic follows a pathway in which resource inputs lead to enhanced clinical capacity and improved outcomes.

Inputs: Newborn: Vayu bCPAP, oxygen blenders, resuscitation equipment, monitors, oxygen concentrators, and consumables. Maternal: hemorrhage quantification and treatment tools, Butterfly ultrasound, Hemocue, heart tone Dopplers, and consumables.Activities: Training in ENCC Parts 1 and 2, Vayu bCPAP training, WHO PPH Course, and basic ultrasound diagnosis training; establishment of facility-based “Champions” and LDHF practice corners. Monthly mentoring, supportive supervision, and scale-up assistance.Outputs: We anticipate timely resuscitation (within one minute) and improved treatment of respiratory distress, in addition to improved maternal risk stratification and management of PPH.Outcomes: We anticipate a reduction in perinatal mortality, improved SCBU neonatal survival, and decreases in PPH incidence, institutional maternal mortality, and morbidity.Impact: We anticipate a sustained reduction in maternal and neonatal mortality and morbidity, contributing to SDG targets.

This implementation logic model is based on the following assumptions:There will be sustained political support for this project.Supply chain systems will ensure maternal and newborn commodity security across supported facilities.Staff will remain committed to project implementation.

The main components of the project plan, as outlined above, are shown in Figure 2.

### 1.4. Objectives

The primary objective of implementing a targeted service delivery bundle is to enhance maternal and newborn outcomes in a cohort of nine hospitals over a three-year period. These service delivery improvements aim to achieve the following:Reduce neonatal mortality: Achieve a 50% reduction in neonatal deaths within the first 24 h and a 10% reduction in intrapartum or “fresh” stillbirths compared to a baseline assessment.Reduce neonatal morbidity: Achieve a 25% reduction in neonatal transfers to advanced care.Improve neonatal clinical practice: Ensure that 80% of SCBU admissions with respiratory distress receive appropriate oxygen therapy.Reduce maternal morbidity: Achieve a 40% reduction in the incidence of postpartum hemorrhage and a 50% reduction in institutional maternal mortality.Improve obstetric clinical practice: Ensure that 90% of deliveries utilize active management of the third stage of labor with uterotonics to prevent hemorrhage.Strengthening diagnostic capacity: Deploy handheld ultrasound and point-of-care hemoglobin testing to improve obstetric risk stratification.Maintain competency: Implement a “train-the-trainer” model, mentoring, low-dose high-frequency practice, and supportive supervision to maintain high performance on knowledge and skills checks at 12-month intervals.

## 2. Materials and Methods

### 2.1. Implementation Design and Timeline

The longitudinal review of this protocol will utilize a Hybrid Type 1 effectiveness-implementation design. This approach allows for the primary review of the clinical effectiveness of the maternal and newborn bundle on patient outcomes, while simultaneously observing and gathering data on its feasibility, acceptability, and sustainability within the targeted facilities. The review employs a prospective, quasi-experimental before-and-after design.

Routinely collected service-delivery data from the three months immediately before implementation will be compared with data from the final three months of the 36-month implementation period, with continuous monitoring throughout. This design was selected for three reasons. First, the bundle is delivered as a facility-level package of training, equipment, mentoring, and supervision; patient-level randomization would not preserve intervention integrity. Second, withholding the bundle from comparable facilities is ethically difficult given Sierra Leone’s mortality burden and the established effectiveness of each component. Third, all participating facilities report to the national District Health Information System 2 (DHIS2), providing a long retrospective time-series that strengthens within-facility comparisons. Limitations arising from the absence of concurrent control are discussed in Section 3.5. Implementation will be divided into three phases:Preparatory Phase: Baseline analysis and equipment procurement. Based on these findings, a causal/bottleneck analysis of the adequacy of perinatal care quality will be conducted and shared with hospital administrations, and mitigation plans will be prepared.Implementation Phase (months 1–18): Training of trainers and equipment deployment. Training scale-up, mentoring, and supportive supervision, to include midwives, nurses, surgical and community health officers, and physicians (2024–2025).Sustainability Phase (months 19–36): Continue supportive supervision and transition to MoHS ownership (2026–2027).

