### 2.6. Data Collection

Data collection is stratified by outcome type:Clinical Data (See Table 2): Quantitative will be collected from existing Ministry of Health (DHIS2) systems and project-specific sources. Project data collectors will collaborate with medical record officers to extract granular clinical data from consecutive maternity and newborn registers across all nine facilities. A preliminary review for validation and missing entries will be followed by cross-verification. Outcomes observed during the implementation and sustainability periods will be compared with retrospective baseline data collected three months prior to training.Implementation and Educational Data (See Table 3): Quantitative implementation metrics, including training logs and low-dose high-frequency (LDHF) practice frequencies, will be extracted from facility-level project registers. Educational indicators, such as performance on objective structured clinical examinations (OSCEs) and skills retention at 12 months, will be collected and tabulated by the mentorship teams.Qualitative data: Qualitative insights regarding implementation barriers and skill retention will be obtained from selected facility staff interviews, debriefs, and surveys.

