### 2.7. Data Analysis

The service delivery bundle will be reviewed as a prospective, observational program assessment using a pre–post design.

Quantitative Analysis: Clinical and implementation indicators (Table 2 and Table 3) from the baseline period (3 months prior to implementation) will be compared with the final period (last 3 months of the project). Data will be analyzed using analysis of variance, unpaired and paired t-tests, and chi-square analysis as appropriate.Qualitative Analysis: Qualitative data from staff interviews and debriefs will be transcribed and subjected to thematic analysis to identify operational bottlenecks and assess the acceptability and feasibility of the service delivery bundle.

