### 3.5. Limitations

The protocol assessment will involve a pre–post design without a control group; therefore, the findings may be influenced by concurrent government programs, hospital maintenance issues, or external factors. Additionally, the reliability of the retrospective baseline data depends on the quality of the historical facility registers; however, this factor will be mitigated by a robust data cleaning and cross-verification process. The contribution of supplies and consumables, both to support the innovations and in addition to IPC and routine supplies, cannot be independently measured.

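### The effect is read from two 3-month windows about three years apart with no term for a pre-existing trend, although the design is justified by a long DHIS2 series

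*Protocol article*

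**What the plan says.** Section 2.1 (Implementation Design and Timeline) sets the comparison: "data from the three months immediately before implementation will be compared with data from the final three months of the 36-month implementation period". The months between the two windows are to be followed by ongoing monitoring, but they have no stated part in the contrast. Section 2.7 (Data Analysis) uses the same two windows for all clinical and implementation indicators and names the methods: "Data will be analyzed using analysis of variance, unpaired and paired t-tests, and chi-square analysis as appropriate". None of these, as described, carries a time trend.

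Section 2.1 gives three reasons for the uncontrolled before-and-after design. The third is that all facilities report to DHIS2, "providing a long retrospective time-series that strengthens within-facility comparisons".

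Section 2.6 (Data Collection) describes another comparison: "Outcomes observed during the implementation and sustainability periods will be compared with retrospective baseline data collected three months prior to training".

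Section 3.5 (Limitations) accepts that there is no control group and that "the findings may be influenced by concurrent government programs, hospital maintenance issues, or external factors". It does not mention a trend already under way before the project, and it offers no analytic remedy.

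**The concern.** A contrast of two points in time cannot tell a bundle effect from a decline that was already in progress. Such a decline is plausible on the article's own account: Section 1.2 describes special care baby units established in 16 districts and national scale-up of Helping Babies Breathe. The long DHIS2 series is the one resource in the plan that could separate the two, and it is cited as a reason why the design is acceptable, but it enters no described analysis. The justification and the analysis do not match.

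Sections 2.1 and 2.7 also estimate the effect at the end of the project, whereas Section 2.6 points to the whole of the implementation and sustainability periods. These are different quantities, and the percentage targets in Section 1.4 do not say which one they refer to.

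**Working it through.** The article states no sample size, power, alpha or trend, so there is no figure of its own to reproduce. Two-sided alpha of 0.05, the trend sizes, the early-death rate and the noise level below are assumptions.

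**Inputs.** Table 1 column sums: 15,536 births and 179 maternal deaths a year. Per 3-month window: 15,536 / 4 = 3,884 births and 179 / 4 = 44.75 maternal deaths. Section 1.4 targets: reductions of 50% (neonatal deaths within 24 h), 10% (fresh stillbirths), 25% (transfers), 40% (PPH) and 50% (institutional maternal mortality).

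**1. Apparent reduction from trend alone.** The window midpoints lie at months −1.5 and 34.5, 36 months apart. For an annual fall r and no bundle effect, the apparent reduction is 1 − (1 − r)³:
- r = 3%: 8.7%
- r = 5%: 14.3%
- r = 8%: 22.1%

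**2. Annual fall that reaches each target unaided.** r = 1 − (1 − target)^(1/3):
- 10% target: 3.5% a year
- 25% target: 9.1% a year
- 40% target: 15.7% a year
- 50% target: 20.6% a year

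**3. How often trend alone is called significant.** Simulated two-window test, assuming 20 early deaths per 1000 births and 15% facility-month noise:

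| Annual fall | Rejections with no bundle effect |
|---|---|
| 0% | about 7% |
| 3% | 11% |
| 5% | 18% |
| 8% | about 32% |

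The 7% with no trend is above 5% because the test ignores the extra noise. The trend accounts only for the increase over 7%.

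**4. Does a segmented model remove the bias?** Simulation with 36 months before and 36 after, Poisson counts, no bundle effect, base rate 3% and a fall of 5% a year: the two-window rate ratio is 0.86 with 21% rejections, and the segmented model gives about 1.00 with 4.5%. Over all scenarios run, the segmented model rejected in 4–6% of runs.

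**5. What the model costs in precision.** Maternal death, true rate ratio 0.50.
- Two windows: SE(log RR) = √(1/44.75 + 1/22.375) = 0.26. The 95% CI is 0.50 × exp(±1.96 × 0.26), or 0.30 to 0.83.
- Rate ratio at months 34–36 against the projected pre-trend (Poisson, level and slope change, no overdispersion): SE about 0.40 with 24 pre-months (calendar-month terms included), 0.25 with 36 and 0.17 with 60. At 24 pre-months the CI is about 0.23 to 1.09.

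**6. The two post-periods.** Suppose that the effect rises linearly over the 18-month Implementation Phase and then stays constant (assumed). The mean share of the full effect over months 1–36 is (Σ m/18 for m = 1 to 18, plus 18) / 36 = (9.5 + 18) / 36 = 0.764. A 50% final effect therefore averages 0.764 × 50% = 38% over the whole period.

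**The case against.** The strongest reply is that this is a programme review which openly admits its missing control, that every trend size above is assumed, and that modelling detail may be left to a fuller plan. The first two points are true. But Section 2.7 fixes the contrast and the family of tests, so the analysis has not been left open, and admitting external influences does not remove a trend that the cited data could help to estimate.

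Some stronger readings are tempting, and the documents do not support them:
- *The headline targets could be met by trend alone.* The 40% and 50% targets would need falls of about 16% and 21% a year. Trend realistically threatens the 10% and 25% targets, and transfers are a secondary outcome in Section 2.4.1.
- *Most of the data are thrown away.* They stay out of the final contrast in Sections 2.1 and 2.7, but they are collected and monitored, and Section 2.6 can be read as using them.
- *Two short windows make the intervals needlessly wide.* Against the model proposed here this fails. With 24 pre-months the model's interval is wider, and only with more than about 36 is it narrower.
- *The baseline is contaminated by the Preparatory Phase.* Section 2.1 gives that phase no dates, so an overlap is inference.
- *Baseline is defined in two ways, before implementation and before training.* These are close to synonymous, since the Implementation Phase opens with training of trainers.
- *Season distorts the contrast.* The two windows fall in the same calendar months, so season is roughly matched.

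**Conclusion.** The point holds as a matter of bias and of internal consistency, not of precision. As written, the plan credits any pre-existing trend to the bundle: 9%, 14% or 22% for assumed falls of 3%, 5% or 8% a year. The chance of a significant result with no bundle effect rises from about 7% to between 11% and 32%, given the assumed event rate and noise. The exposure is greatest for the fresh-stillbirth and transfer targets and small for the 40% and 50% targets. Separately, Section 2.6 conflicts with Sections 2.1 and 2.7 on the post-period; under an assumed 18-month linear ramp, the same effect reads as 50% or 38%. The size of any real trend cannot be judged from the article.

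**What to change.** 1. For outcomes with usable DHIS2 or register history, make the primary analysis a monthly interrupted time series of facility counts with facility effects, a pre-trend, and level and slope change, allowing for overdispersion. Use at least 36 pre-implementation months where available.
2. State one estimand: the rate ratio at months 34–36 against the projected pre-trend.
3. Keep the two-window contrast as descriptive, and as the only analysis for outcomes without history. Name those outcomes; the article does not say, for example, whether deaths under 24 h or PPH of 500 mL have a usable DHIS2 history.
4. Align Section 2.6 with Sections 2.1 and 2.7.

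The cost is analysis wording and an extract of months that already exist; no care changes. The downsides should be stated in the plan. Projecting the pre-trend costs variance (SE about 0.40, 0.25 and 0.17 with 24, 36 and 60 pre-months, against 0.26 for two windows), and overdispersion would add to it. Results will depend on DHIS2 completeness before the project. The model also assumes that the pre-trend would have continued, so it does not remove the influence of a concurrent programme that starts during the project; Section 3.5 should keep that limitation.

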**Figure 2 mps-09-00096-f002:**
[figure not shown]
Implementation logic model.

**Table 1 mps-09-00096-t001:** Baseline characteristics and target training populations of participating healthcare facilities (2023).

Facility Name	Location (City)	Number of Annual Births	Maternal Deaths (2023)	Neonatal Deaths (2023)	Number of Annual C/S	Healthcare Workers Trained in Past 2 Years	Total Healthcare Workers to Be Trained
Bo Government Hospital	Bo	3226	34	191	1053	28	23
Jenner Wright Clinic	Freetown	412	17	6	14	13	-
King Harman Road Government Hospital	Freetown	712	8	15	331	9	87
Kissy CHC	Freetown	440	17	4	3	19	-
Princess Christian Maternity Hospital	Freetown	7099	63	464	3016	12	125
Rokupa Government Hospital	Freetown	1495	1	54	599	5	65
Ross Road CHC	Freetown	626	3	1	3	29	-
St. Anthony’s CHC	Freetown	511	19	2	5	27	-
Waterloo CHC	Waterloo	1015	17	11	20	8	23

**Table 2 mps-09-00096-t002:** Education and training.

Category	Indicator	Definition
Training uptake	Number of healthcare workers trained	Total number of midwives, nurses, physicians, and other staff completing WHO ENCC and PPH training modules
	Training completion against targets	Number completing training/facility training target
Skills retention	Frequency of LDHF practice sessions	Number of documented low-dose, high-frequency practice sessions per facility
	OSCE performance scores	Percentage of participants achieving competency on Objective Structured Clinical Examinations (OSCEs)
	Skills retention at 12 months	Percentage of trained staff maintaining competency at 12-month reassessment
Mentorship and supervision	Mentorship visits completed	Number of supportive supervision and mentorship visits conducted per facility
	Practice corner utilization	Frequency of use of facility-based LDHF practice stations

**Table 3 mps-09-00096-t003:** Maternal and newborn measures with definitions.

Category	Indicator	Definition
Maternal indicators	PPH incidence (500 cc)	[# of PPH incidence (500 cc)]/[total births]
	Uterotonics used for PPH prevention	[# of uterotonics used for PPH prevention]/[total births]
	Direct obstetric case fatalities	[# maternal deaths]/[# of total births]
	Admission triage scans	[# of ultrasound scans]/[# of maternal admissions]
	Abnormal scan findings	[# of abnormal scans]/[# of scans]
Neonatal indicators	Fresh stillbirths	[# of fresh stillbirths]/[total births]
	Neonatal case fatality rate < 24 h	[# of neonatal deaths < 24 h]/[total births]

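### The design is defended by within-facility comparison, but targets, outcome ratios and tests never fix facility as stratum or pair, so a changed facility mix of births could be read as a bundle effect

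*Protocol article*

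**What the plan says.** - **Rationale.** Section 2.1 gives three reasons for a before-and-after design without a concurrent control. The third is that every facility reports to the national system, "providing a long retrospective time-series that strengthens within-facility comparisons".
- **Targets.** Section 1.4 sets one figure per outcome for the nine facilities together: 50% fewer neonatal deaths within 24 h, 10% fewer fresh stillbirths, 40% less postpartum hemorrhage (PPH) and 50% lower institutional maternal mortality.
- **Outcome ratios.** Table 3 defines the neonatal primary as the number "of neonatal deaths < 24 h]/[total births", maternal fatality as "maternal deaths]/[# of total births" and PPH as "of PPH incidence (500 cc)]/[total births". It does not say whether a ratio is formed per facility or for the network. The special care baby unit (SCBU) indicators use admissions as denominator and are not part of this point.
- **Analysis.** Section 2.7 says that indicators "from the baseline period (3 months prior to implementation) will be compared with the final period (last 3 months of the project", and then: "Data will be analyzed using analysis of variance, unpaired and paired t-tests, and chi-square analysis as appropriate". It names no unit, pair, stratum or weight.
- **Limitations.** Section 3.5 names the missing control group, concurrent programs and external factors. It does not mention a change in where births take place.

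**The concern.** The main defense of an uncontrolled design is that each facility serves as its own comparison. That holds only if the analysis conditions on facility. A ratio of all events to all births does not: it mixes change inside facilities with change in the share of births each facility takes. The windows lie about three years apart, and new equipment, supplies and triage could change where women deliver or bring new women in. If the facilities have very different event rates, such a change moves the pooled ratio and is credited to the bundle, or hides its effect. It can also move the neonatal and maternal results in opposite directions.

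**Working it through.** The plan states no pooled rate, power or significance level, so there is no figure to reproduce. The check uses the 2023 counts in Table 1.

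**Inputs (births / neonatal deaths / maternal deaths)**

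| Group | Births | Neonatal | Maternal | Neonatal per 1000 | Maternal per 100,000 |
|---|---|---|---|---|---|
| Tertiary hospital | 7,099 | 464 | 63 | 65.4 | 887 |
| Bo | 3,226 | 191 | 34 | 59.2 | 1,054 |
| Three smaller hospitals (712 + 1,495 + 1,015 births) | 3,222 | 80 | 26 | 24.8 | 807 |
| Four CHCs (412 + 440 + 626 + 511 births) | 1,989 | 13 | 56 | 6.5 | 2,815 |
| All nine | 15,536 | 748 | 179 | 48.1 | 1,152 |

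The tertiary share of births is 7,099/15,536 = 45.7%; the CHC share is 1,989/15,536 = 12.8%. By single facility, neonatal rates run from 1.6 (1/626) to 65.4 per 1000. A chi-square test for equal rates gives 178 on 8 df for neonatal deaths and 115 on 8 df for maternal deaths.

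**Formula.** Pooled rate = sum over facilities of (birth share x facility rate). Facility rates are held fixed and only the shares change.

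**Case A: births enter from outside the network.** CHC births double with new women at the present CHC rates.
- Neonatal: (748 + 13)/(15,536 + 1,989) = 761/17,525 = 43.4 per 1000, a change of -9.8%.
- Maternal: (179 + 56)/17,525 = 235/17,525 = 1,341 per 100,000, a change of +16.4%.
- Split: the CHC share rises from 12.8% to 3,978/17,525 = 22.7%. The five hospitals together have 735/13,547 = 54.3 neonatal deaths per 1000. The share component is 0.099 x (6.5 - 54.3) = -4.7 per 1000, which is the whole crude change. The rate component is zero.

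No woman changes facility here, so the result does not depend on who carries what risk from one site to another.

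**Case B: births move among the nine.** The tertiary share falls by 10 points (1,554 births), and moved women take the receiving site's rate. Neonatal change = 0.10 x (receiving rate - 65.4)/48.1.

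| Births go to | Receiving rate per 1000 | Neonatal | Maternal |
|---|---|---|---|
| Other eight, in proportion | 284/8,437 = 33.7 | -6.6% | +4.2% |
| Three smaller hospitals | 24.8 | -8.4% | -0.7% |
| Four CHCs | 6.5 | -12.2% | +16.7% |

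The reverse of the last shift gives +12.2% and -16.7%. With 15,536/4 = 3,884 births per window, a two-proportion test on the three neonatal shifts has z = 0.66, 0.85 and 1.25. A nominal 5% test would then reject in about 10%, 14% and 24% of evaluations. Deaths within 24 h are a subset of these deaths, so at the same relative shift the figures for the actual primary outcome would be lower.

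**Case C: births move among the nine and each woman keeps her own risk.** Total deaths and total births are unchanged, so the pooled ratio stays at 48.1 per 1000 while facility rates change. If the women who move up from the CHCs have a risk between 6.5 and 65.4 per 1000, the CHC and tertiary rates both fall, although nothing has improved.

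**The case against.** **The level is not stated.** A reader might infer that the outcomes are network ratios. No passage says so. Section 2.1 points to within-facility comparison, 2.7 allows paired t-tests, and 2.8 says data are aggregated by facility. A paired comparison of facility rates would not depend on birth shares. This objection stands, and the point is therefore that the level is left open while the rationale depends on it. It does not remove the point. The targets are single cohort figures, which read most naturally as pooled. An unweighted paired test over nine facilities would give a CHC with 412 births (2.7%) the same weight as the tertiary hospital with 45.7%, so it would not estimate those targets. Detail may be left to an analysis plan, but here the article's stated rationale and its stated analysis do not meet.

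**Case mix.** A reader might infer that any shift in place of delivery moves the result with no change in care. Within the nine facilities that requires moved women to take the receiving site's rate. Section 2.2 says the CHCs perform no cesareans and do not care for small or sick newborns, so much of the spread is plausibly case mix. Under Case C the crude ratio is sound and the stratified one misleads. This stands. It limits Case B, but not Case A.

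**The data.** Table 1 counts all neonatal deaths and does not say where deaths of transferred babies are recorded. Maternal deaths exceed neonatal deaths at all four CHCs, and Table 1 lists cesareans at CHCs said to perform none. The maternal shifts need caution.

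**Size.** Ten points is 22% of tertiary births (1,554/7,099), a large shift. A reader might set the 7-12% against the 10% stillbirth target, but no facility stillbirth rates are given. Moving every tertiary birth to the other seven Greater Freetown sites would still not halve the neonatal rate: 7,871 moved births would be needed.

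**Conclusion.** The point holds in a limited form. The plan rests its uncontrolled design on within-facility comparison and then fixes no analysis that makes one. If the birth-based ratios are pooled, a change in facility mix enters the estimate. The firmest illustration is uneven growth from outside the network: doubling CHC births gives -9.8% neonatal and +16.4% maternal, assuming the new women have the present CHC rates. A 10-point fall in the tertiary share gives about -7% to -12% neonatal, but only if moved women take on the receiving site's rate.

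These are illustrations on a proxy. The documents do not show many-fold differences between facilities for deaths within 24 h, PPH or fresh stillbirth, and they do not show that any shift will occur. The shifts are well below the 40-50% targets and could not produce those alone. They could distort a more modest observed change, and they leave the within-facility claim in 2.1 without support.

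**What to change.** In 2.7, for each birth-based clinical outcome:

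1. State the level of the ratio and keep the crude nine-facility change as the headline.
2. Add a facility-stratified comparison, for example rates standardized to the mean birth shares of the two windows, or a facility-stratified test.
3. Report births by facility in both windows, with the part of the crude change that is due to birth shares.
4. Claim improved care within facilities only when the crude and stratified results agree, and not from the stratified component alone. This guards against both errors: in Case A the crude result moves and the stratified one does not, and in Case C the reverse.

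The cost is a little more analysis on facility counts that 2.6 and 2.8 already provide for. The downside is that the stratified result is itself distorted if high-risk women move between facilities, which is why it stands beside the crude result and does not replace it.
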